#### *Data analyses*

The primary analysis, which will utilize data at the cluster level, will be based on an alternative to a classic randomization test which involves a two stage approach [42]. First, a linear model is fit with the cluster as the analysis unit and the composite mortality/morbidity rate for each cluster as the outcome. In the second stage, the residuals from the first stage model and the t-test procedures [42] will be used to generate a hypothesis test of the difference in composite mortality/morbidity and to generate 95% confidence intervals for the difference in this rate between the two treatment arms, controlling for site and randomization stratum.

To facilitate the model-based primary analysis, we will evaluate baseline differences in key demographic and clinical measures between the intervention and control clusters to assess the extent, if any, of baseline imbalances between the two groups that might confound study inferences. If baseline differences are identified, we will include appropriate cluster-level or individual-level variables to evaluate the impact of these variables on the observed treatment effect. Because the primary interest is in the increase in the marginal morbidity/mortality rate at the cluster level, the generalized estimating equations method [26] will be used for the primary analysis. The model will control for cluster-level effects by assuming country-specific within-country correlation within clusters, and all inferences will be based on the empirical correlation matrix [26].

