**Methods/Design:**

This multi-country cluster randomized trial will assess the impact of antenatal ultrasound screening performed by health care staff on a composite outcome consisting of maternal mortality and maternal near-miss, stillbirth and neonatal mortality in low-resource community settings. The trial will utilize an existing research infrastructure, the Global Network for Women’s and Children’s Health Research with sites in Pakistan, Kenya, Zambia, Democratic Republic of Congo and Guatemala. A maternal and newborn health registry in defined geographic areas which documents all pregnancies and their outcomes to 6 weeks post-delivery will provide population-based rates of maternal mortality and morbidity, stillbirth, neonatal mortality and morbidity, and health care utilization for study clusters. A total of 58 study clusters each with a health center and about 500 births per year will be randomized (29 intervention and 29 control). The intervention includes training of health workers (e.g., nurses, midwives, clinical officers) to perform ultrasound examinations during antenatal care, generally at 18–22 and at 32–36 weeks for each subject. Women who are identified as having a complication of pregnancy will be referred to a hospital for appropriate care. Finally, the intervention includes community sensitization activities to inform women and their families of the availability of ultrasound at the antenatal care clinic and training in emergency obstetric and neonatal care at referral facilities.

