## Methods/Design

The cluster-randomized controlled trial (RCT) will be undertaken to address two important hypotheses. The primary hypothesis is that antenatal ultrasound screening at antenatal clinics (ANC) will improve a composite outcome of maternal mortality, maternal near miss, stillbirth, and neonatal mortality. Two important secondary hypotheses (which will be assessed independently without adjustment for multiple comparisons) that the study has been powered to test is that ultrasound will increase 1) the rate of prenatal care utilization and 2) utilization of health facilities for delivery by for women with complicated pregnancies. Additional secondary outcomes include the difference between ultrasound and non-ultrasound clusters in rates of maternal mortality, maternal morbidity, neonatal deaths, intra-uterine growth restriction-related mortality, and intrapartum stillbirths. Because the effectiveness of training is an important consideration for implementation, an additional part of the study is evaluation of the training component.

The trial will be undertaken in five LIC rural settings. The study design is a cluster RCT with intervention and control clusters stratified by country, while also considering factors such as historic perinatal mortality rates and logistic factors such as travel time to Emergency Obstetric and Neonatal Care facilities. Each ultrasound cluster will be defined by a health center and its catchment area and generally have approximately 500 births per year. The clusters will be stratified by country and then randomized to the intervention group or to the control group.

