#### *Sample size considerations*

The primary outcome is a composite of four components (stillbirth, neonatal mortality, maternal mortality, and maternal near miss). Within the Global Network, the neonatal rates average about 27 per 1,000 births, the stillbirth rates average about 33 per 1,000, and the maternal mortality is approximately 2 per 1,000 births [37,40,41]. While we have not analyzed Global Network maternal near miss data, studies suggest that for every maternal death there are 5 to 10 near misses and we estimate that the maternal near miss rate within the Global Network is 20 to 30 per 1,000 births. This estimate coincides with several developing country estimates of near misses ranging from 2% to 3% of all pregnancies. For sample size calculations we assumed a near miss rate of 25 per 1,000 births. Thus, our composite outcome baseline rate is estimated to be in the range of 80 to 90 events per 1,000 pregnancies with current care in the trial clusters.

Sample size estimates for potential decreases in the composite maternal, fetal, and neonatal outcomes with 90% power and alpha at 0.05 for rates of the composite outcome in the range of 70 to 90 events per 1000 deliveries, target reductions of 20% to 25%, an intra-cluster correlation (ICC) of 0.005 (a rate that is consistent with historic Global Network mortality rates). Based on the power calculations with these assumptions, 58 clusters will provide more than 80% power to detect a 25% improvement in the composite outcome over a range of assumptions that are reasonable based on historic MNH Registry data; the design will provide 79% to 94% power to detect as little as a 20% reduction over the range of underlying risks.

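### Beyond site and stratum, covariates are added only on observed baseline imbalance; each cluster's pre-trial stillbirth plus neonatal mortality rate should be a fixed covariate instead

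*Protocol article*

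**What the plan says.** The Data analyses section describes a two-stage cluster-level analysis whose comparison is made "controlling for site and randomization stratum". Those two terms do not depend on balance.

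The next paragraph adds a check, introduced as serving the model-based primary analysis: "we will evaluate baseline differences in key demographic and clinical measures between the intervention and control clusters". Its consequence is: "If baseline differences are identified, we will include appropriate cluster-level or individual-level variables". The purpose given is to see what those variables do to the estimated effect. The same paragraph then names generalized estimating equations (GEE) as the primary method.

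The Methods/Design section stratifies the randomization by country and names other matters weighed at allocation: "factors such as historic perinatal mortality rates and logistic factors such as travel time to Emergency Obstetric and Neonatal Care facilities". The abstract says that the registry "will provide population-based rates of maternal mortality and morbidity, stillbirth, neonatal mortality and morbidity, and health care utilization for study clusters", and the sample size section refers to assumptions "over a range of assumptions that are reasonable based on historic MNH Registry data". No section makes a cluster's historic rate a fixed covariate in the analysis.

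**The concern.** The value of adjusting for a covariate in a randomized comparison comes from how well it predicts the outcome, not from whether the arms happen to differ on it. A rule triggered by imbalance has two costs. The reported effect depends on a judgement made after looking at the arms. And when the arms look similar, which is the usual result of randomization, the precision from a prognostic covariate is lost.

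With 58 clusters and cluster-level inference, variation between clusters dominates the standard error, so a baseline cluster rate is where precision might be found cheaply. The wording also leaves open which estimate would be reported as primary if differences were seen.

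**Working it through.** **Inputs from the article.** 29 clusters per arm; about 500 births per cluster per year (m); ICC 0.005; alpha 0.05; composite rate 70 to 90 per 1,000; reduction 20%. Component rates per 1,000: neonatal death 27, stillbirth 33, maternal death 2, near miss 25, in total 27 + 33 + 2 + 25 = 87. Stillbirth plus neonatal death is 60 of these 87.

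**Assumptions.** Two-sided test; one year of births; equal cluster sizes; ICC 0.005 taken as wholly residual after country; country as the only stratum, so 58 − 6 = 52 degrees of freedom.

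**1. Power without the covariate.** Var(cluster rate) = p(1 − p)[ICC + (1 − ICC)/m], and the bracket is 0.005 + 0.995/500 = 0.00699. At 87 per 1,000 and a 20% reduction, p1 = 0.0870 and p2 = 0.0696. SE = √[(0.07943 + 0.06476) × 0.00699/29] = 0.00590. The noncentrality is 0.0174/0.00590 = 2.95, and power by noncentral t is 82.6%. At 70, 80 and 90 per 1,000 it is 73.1%, 79.0% and 83.9%. The article states 79% to 94% for a 20% reduction. That range did not reproduce under these inputs, which is a separate matter.

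**2. How far a historic mortality rate can predict the composite.** The reliability of a one-year cluster rate is ICC/[ICC + (1 − ICC)/m] = 0.005/0.00699 = 0.715. Let c be the year-to-year correlation of true cluster rates, which the article does not give. Take near-miss cluster effects as independent of mortality, and leave out the small maternal death component. The mortality share of between-cluster variance is then 0.060 × 0.940/(0.060 × 0.940 + 0.025 × 0.975) = 0.0564/0.0808 = 0.70. The correlation of the historic rate with the trial rate is r = 0.715 × c × √0.70 = 0.598c.

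**3. Power with the covariate always in.** Multiply the variance by 1 − r² and use 51 degrees of freedom (20% reduction):

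| c | r | r² | Power at 70 per 1,000 | Power at 87 per 1,000 |
|---|---|---|---|---|
| no covariate | – | – | 73.1% | 82.6% |
| 0.2 | 0.12 | 0.01 | 73.7% | 83.1% |
| 0.3 | 0.18 | 0.03 | 74.5% | 83.7% |
| 0.5 | 0.30 | 0.09 | 77% | 86% |
| 0.7 | 0.42 | 0.17 | 81% | 89% |
| 0.9 | 0.54 | 0.29 | 86% | 93% |

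**4. What an imbalance trigger recovers.** A simulation (8,000 runs per setting, 29 against 29 clusters, 80 per 1,000, 20% reduction) compared adjusting only when the baseline difference had p < 0.05 with always adjusting. The threshold is an assumption. Here ρ is the correlation between observed baseline and trial rates, so it corresponds to r above, not to c.

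| ρ | Power, triggered | Power, always | Type I error, triggered |
|---|---|---|---|
| 0 | 79.4% | 78.9% | 4.6% |
| 0.3 | 79.3% | 81.7% | 4.8% |
| 0.5 | 79.4% | 88.0% | 4.1% |
| 0.7 | 81.2% | 96.9% | 3.8% |

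The trigger fires in about 5% of trials, so it recovers almost none of the gain. Always adjusting costs under 1 point when the covariate is useless. Under step 2, r cannot exceed 0.598 even at c = 1, so the last row is beyond what one baseline year could give.

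**The case against.** **The clause may already be a sensitivity analysis.** Its stated purpose is to assess how the variables affect the observed effect, which reads that way. Its introduction ties it to the primary analysis, which reads the other way. The ambiguity stands and should be settled.

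**Historic mortality may already be in the model.** If it helps define the strata, the stratum term captures part of the gain. The article mentions it as a consideration and then describes stratification by country alone, so this is unresolved. The power figures give no credit for it.

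**The gain rests on assumptions.** At c = 0.2 to 0.3 it is about 1 point or less at 87 per 1,000. If the ICC left after country and stratum were 0.0025 (an assumption), unadjusted power would be 89.5% at 70 and 95.1% at 87 per 1,000, and c = 0.5 would add only about 1 to 1.5 points. This stands.

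**Detail belongs in the analysis plan.** The absence of a variable list or threshold in a condensed article is no finding. The point concerns the rule that the article does state.

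A reader might also infer stronger things that the documents do not support:

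- That no covariate enters unless the arms differ: site and stratum always enter.
- That individual-level variables cannot be used: they cannot enter the cluster-level first stage as they stand, but GEE, also called primary, can take them.
- That the type I error is inflated: with a single covariate the trigger was slightly conservative. An open list of covariates was not tested.
- That historic mortality is the best available predictor, or that adjustment would repair a power shortfall: neither is documented.
- That every cluster's history is in hand: this is implied, but Table 3 gives country figures only. DRC, 8 of 58 clusters, has no 2009–2010 birth count, and the table footnote cites 2006–2007 data and a 7-day neonatal rate.

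**Conclusion.** The point holds as a cheap improvement to a stated rule, not as an error that invalidates the test. Conditioning further adjustment on observed imbalance leaves analyst choice in the estimate and gives up most of the precision from a prognostic baseline covariate. For a 20% reduction at 87 per 1,000, fixed adjustment moves power from about 83% to somewhere between 83% and 93%, over year-to-year correlations of 0.2 to 0.9. The size rests on that undocumented correlation, on one baseline year of about 500 births per cluster, on ICC 0.005 being residual, and on historic mortality not already defining the strata. The downside if the covariate proves uninformative is under 1 point of power.

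**What to change.** In the Data analyses section:

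1. Prespecify each cluster's pre-trial stillbirth plus neonatal mortality rate, centred within country, as a fixed covariate beside site and randomization stratum. Keep it whatever the balance, in whichever of the two named models is confirmed as primary.
2. Say that any adjustment prompted by observed baseline differences is a sensitivity analysis and does not replace the primary estimate.
3. State a rule for clusters without comparable history, chiefly the 8 in DRC. One option is the country mean, which gives those clusters a centred value of zero.
4. Say whether historic perinatal mortality defines the randomization strata, since this determines how much the covariate can add.

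The cost is one degree of freedom (52 to 51 on the assumptions above), a substitute value for DRC, extraction of cluster-level registry rates, and a change of wording.

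### Two different methods, a cluster-level residual t-test and a GEE, are each named as the primary analysis, with no rule for which one decides the trial

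*Protocol article*

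**What the plan says.** All of this is in the Data analyses section of the protocol article, in two consecutive paragraphs.

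- **First paragraph.** "The primary analysis, which will utilize data at the cluster level, will be based on an alternative to a classic randomization test". A linear model is fitted to cluster composite rates; then "the residuals from the first stage model and the t-test procedures [42] will be used to generate a hypothesis test". The same step gives a 95% confidence interval for the between-arm difference in rates, "controlling for site and randomization stratum".
- **Second paragraph.** After describing a check for baseline imbalance, it says that "the generalized estimating equations method [26] will be used for the primary analysis". The correlation is modelled by "assuming country-specific within-country correlation within clusters, and all inferences will be based on the empirical correlation matrix". On covariates: "If baseline differences are identified, we will include appropriate cluster-level or individual-level variables". The reason given for the GEE is an interest "in the increase in the marginal morbidity/mortality rate at the cluster level".

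Methods/Design states a single primary hypothesis: "The primary hypothesis is that antenatal ultrasound screening at antenatal clinics (ANC) will improve a composite outcome". Sample size considerations gives a single alpha of 0.05.

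**The concern.** One hypothesis and one alpha call for one deciding test. Here two procedures carry the primary label, and they are not the same calculation in different words:

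- The unit is the cluster rate in one. The other models correlation within clusters and may take individual-level covariates.
- Clusters are weighted differently, except in special cases such as equal cluster sizes.
- One uses a pooled residual variance and a t distribution; the other uses an empirical variance.
- One estimates a difference in rates; no link or effect measure is given for the GEE.

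If the two results fall on opposite sides of 0.05, the document does not say whether the trial succeeded. Covariates that enter only after imbalance has been seen leave a further choice open in the model-based version.

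**Working it through.** **Step 1: can the two passages be read as one?** The most charitable reading is that the GEE is a covariate-adjusted companion to the t-test. The second paragraph rules this out. It gives the GEE the primary role outright, justifies it by the main interest of the trial, and rests all inference on the empirical matrix. Nothing elsewhere in the article ranks the methods. The citation does not help: the GEE is referenced to [26], a number that the Previous research section uses for studies of psychological benefit and facility use, so it may be misnumbered.

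**Step 2: inputs for sizing the consequence.** The plan gives no error rate for either analysis, so there is no figure of its own to reproduce.

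- From the documents: 58 clusters, 29 per arm; 18/10/12/10/8 by country (Table 3); about 500 births per cluster-year; ICC 0.005; country mortality rates from Table 3; near miss 25 per 1,000; alpha 0.05.
- Assumed: two-sided test; one year's births per cluster; the same near-miss rate in every country; beta-binomial outcomes; cluster-size CV of 0 or 0.5; logit link, normal reference and no small-sample correction for the GEE, with correlation estimates truncated at zero.

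**Step 3: anchor.** Effective n per arm = 29 × 500 / (1 + 499 × 0.005) = 14,500 / 3.495 = 4,149. For 80 against 64 per 1,000, SE = √[(0.08 × 0.92 + 0.064 × 0.936) / 4,149] = 0.00567 and z = 0.016 / 0.00567 = 2.82. Power is Φ(2.82 − 1.96), about 80.5%. The simulated t-test has about 82-83% power for a 20% reduction with equal cluster sizes, so the set-up is in line with the design.

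**Step 4: results.** Both tests were run on the same 8,000 simulated trials per row. The columns from *t-test* to *disagree* are under no effect; the last column is under a 20% reduction. All entries are percentages except CV.

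| GEE correlation | CV | t-test | GEE | either | disagree | disagree, 20% reduction |
|---|---|---|---|---|---|---|
| country-specific | 0 | 5.9 | 12.8 | 13.4 | 8.2 | 7.3 |
| country-specific | 0.5 | 6.0 | 14.0 | 14.7 | 9.4 | 10.2 |
| common | 0 | 6.5 | 7.6 | 7.6 | 1.1 | 1.6 |
| common | 0.5 | 5.5 | 7.0 | 7.5 | 2.4 | 5.1 |
| independence | 0 | 5.9 | 6.9 | 6.9 | 1.0 | 1.7 |
| independence | 0.5 | 6.3 | 8.1 | 10.0 | 5.6 | 10.8 |

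A separately coded repeat gave about 5-7% for the t-test, 7-8% or about 13% for the GEE, 7-14% for either, and disagreement of 1-9% under the null and 2-12% under a 20% reduction. The ranges quoted elsewhere pool the two sets.

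**Step 5: where the excess comes from.** Split (either − t-test) into (GEE − t-test) plus (either − GEE):

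- Country-specific, CV 0: 13.4 − 5.9 = 7.5 points, of which 12.8 − 5.9 = 6.9 is the GEE's own excess and 0.6 comes from choosing.
- Country-specific, CV 0.5: 14.7 − 6.0 = 8.7 points; 8.0 is the GEE and 0.7 is choosing.
- Independence, CV 0.5: 10.0 − 6.3 = 3.7 points; 1.8 is the GEE and 1.9 is choosing. This is the one row where choosing contributes about half.

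Referring the GEE to a t distribution with 52 df only lowers the country-specific figures to 11.8% and 13.0%. Each correlation is estimated from just 8 to 18 clusters.

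**Step 6: the t-test's small excess.** A two-sample t-test on residuals counts 58 − 2 = 56 df. With five country terms and arm fitted, the residual df is 58 − 5 − 1 = 52. The statistic is then too large by √(56/52) = 1.038, so the critical value of 2.003 acts like 2.003 / 1.038 = 1.930. On 52 df that has a two-sided p of 0.059, which matches the table. Counting the fitted strata in the df removes this excess.

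**The case against.** The labelling conflict itself has no good answer in the document. An unseen SAP may settle it, but the article is not silent here: it names two primaries, and a SAP that chose either would contradict one published sentence. The other side has more force on size and remedy.

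- **A reader might infer that success may be claimed on either test, with a type I error near 14%.** The document states no such rule. The defect is ambiguity, and the either-test figure shows only what would follow if the ambiguity were exploited. It is also the top of a range that starts near 7%, although the country-specific structure behind the top end is the closest reading of the text.
- **A reader might blame choosing between tests for the whole excess.** Step 5 shows that with country-specific correlation nearly all of it is the GEE's own inflation, which would remain if the GEE alone were primary.
- **The plan gives a reason only for the GEE,** namely interest in the marginal rate. That is fair, so the GEE remains a legitimate choice if its small-sample behaviour is dealt with.
- **It is tempting to prescribe 52 df.** That assumes country is the only stratum. The text lists site and randomization stratum separately, and Methods/Design mentions historic perinatal mortality and travel time as considerations.
- **A reader might take the word *increase* in the GEE rationale as a reversed hypothesis.** It is a wording slip. The hypothesis and the sample size section both make clear that a reduction is sought, and no test or estimate changes.

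**Conclusion.** The point holds as a contradiction on the page: the trial's single confirmatory analysis is defined twice, differently, without precedence. That conclusion needs no simulation. The consequence is material but can be given only as a range. The two methods would return different verdicts in about 1-9% of trials with no effect and about 2-12% with a 20% reduction. Null rejection is about 5-7% for the t-test, about 7-8% or 13-14% for the GEE depending on its correlation structure, and about 7-15% for at least one of the two. These figures rest on the Step 2 assumptions, above all the uncorrected GEE variance. They show the plausible scale of the divergence and are not an estimate of this trial's error rate. It must be resolved before outcome data are seen.

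**What to change.** Name one method as the sole confirmatory analysis and label the other supportive, in the same words in the protocol and the SAP.

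- **Natural choice:** the cluster-level t-test controlling for site and randomization stratum. It is the more fully described of the two and holds close to 5%. Derive its degrees of freedom from the strata actually used.
- **If the GEE is preferred:** state the link and effect measure, the working correlation and a small-sample correction. Confine covariates chosen after imbalance is seen to supportive models.
- **Minor wording:** change *increase* to *difference* in the GEE rationale and check reference [26].

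The cost is a text amendment before data are seen. Recruitment, data collection and sample size are untouched.

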### Ethics approval

The study protocol has been reviewed and approved by ethics review committees including the University of Washington (Seattle, WA), Columbia University (NY, NY), Research Triangle Institute (Durham, NC), University of Zambia (Lusaka, Zambia), Kinshasa School of Public Health (Kinshasa, DRC), Moi University (Eldoret, Kenya), Aga Khan University (Karachi, Pakistan), and Francisco Marroquin University (Guatemala City, Guatemala).

The study sites are clusters in rural areas in Chimaltenango, Guatemala, Lusaka District, Zambia, Equateur Provence, Democratic Republic of Congo; Western Provence, Kenya, and Thatta District, Pakistan. In these areas, over half of the births occur at home (Table 3). The trial will use the Global Network’s Maternal Newborn Health (MNH) pregnancy registry to collect outcome data, as described elsewhere [37]. Based on the sample size described below, we plan to implement the study in a total of 58 clusters (29 intervention and 29 control).

**Table 3 T3:** Ultrasound trial sites

	**Chimaltenango Guatemala**	**Lusaka Zambia**	**Western Provence Kenya**	**Thatta Pakistan**	**DRC**
**Study Clusters* (N)**	18	10	12	10	8
**Births 2009-2010** (N)**	10,706	14,154	17,541	25,909	NA

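### The GEE named as the second primary analysis, with a separate correlation per country and empirical variance, does not hold its 5% level

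*Protocol article*

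**What the plan says.** The Data analyses section of the protocol article describes two analyses and calls each of them primary.

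- The first is a two-stage cluster-level procedure. A linear model is fitted to the cluster rates, and its residuals then give a t-type test and a 95% confidence interval, with adjustment for site and randomization stratum.
- The second comes in the next paragraph, where the "generalized estimating equations method [26] will be used for the primary analysis". Its structure is fixed in one sentence: "assuming country-specific within-country correlation within clusters, and all inferences will be based on the empirical correlation matrix". I read this as one within-cluster correlation estimated for each country, with inference on the empirical (sandwich) variance. The text names no country terms, reference distribution or small-sample correction for the GEE.

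The Ethics approval section says "we plan to implement the study in a total of 58 clusters (29 intervention and 29 control", and Table 3 splits these as Guatemala 18, Zambia 10, Kenya 12, Pakistan 10 and DRC 8. Methods/Design says that clusters "generally have approximately 500 births per year". Sample size considerations uses "an intra-cluster correlation (ICC) of 0.005" and an alpha of 0.05.

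**The concern.** A correlation estimated from 8 to 18 clusters is very imprecise. If a country's clusters happen to look alike, its estimated correlation falls towards zero. The GEE then gives those clusters a large weight at the moment when their residuals are small. The sandwich variance is built from those same residuals, so it comes out too small. This adds to the ordinary small-sample bias of the sandwich with 58 clusters.

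If this GEE served as the confirmatory test, its false-positive rate would exceed 5% and its 95% confidence intervals would be too narrow. A positive result on the composite could not be read at the stated level.

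**Working it through.** **Plan's own figure.** The article gives no type I error for the GEE, only the nominal alpha of 0.05, taken here as two-sided. Its stated power (79% to 94% for a 20% reduction) is a separate matter and this point does not rest on it.

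**Inputs from the article.** Cluster counts 18/10/12/10/8 (Table 3), randomized 1:1 within country; ICC 0.005; near miss 25 per 1,000. The composite rate per 1,000 is neonatal deaths + stillbirths + maternal mortality ratio/100 + 25:

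- Guatemala: 27 + 22 + 0.95 + 25 ≈ 75
- Zambia: 22 + 27 + 2.11 + 25 ≈ 76
- Kenya: 16 + 20 + 0.88 + 25 ≈ 62
- Pakistan: 45 + 54 + 2.39 + 25 ≈ 126
- DRC: 27 + 23 + 5.40 + 25 ≈ 80

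**Assumptions.** 500 births per cluster, because the accrual period is not given. Variation in cluster size is also not given; equal and unequal sizes were tried.

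**Step 1: how unstable the weights are.** A cluster of m births has weight proportional to m/[1 + (m − 1)ρ]. At ρ = 0.005 the denominator is 1 + 499 × 0.005 = 3.495, so the weight is 500/3.495 ≈ 143. If the estimated ρ is zero the weight is 500, which is 3.5 times as much. On a normal approximation, a between-cluster variance estimated from K clusters has a coefficient of variation of about √(2/(K − 1)). That is √(2/7) = 0.53 for 8 clusters and √(2/17) = 0.34 for 18, against √(2/57) = 0.19 for all 58 pooled. In simulation at ICC 0.005 with Table 3 rates, at least one country had an estimated correlation of zero or less in about 10% of trials without country terms and 19% with them.

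**Step 2: simulated type I error.** Beta-binomial outcomes under the null; logit GEE with moment-estimated exchangeable correlations; 3,000 to 6,000 trials per scenario; Monte Carlo standard error about 0.5 points. The GEE code was checked against a standard package for a common correlation, and the standard error was 0.1162 in both. Ranges are across separately coded runs at ICC 0.005 with Table 3 rates or close to them.

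| Analysis at nominal 5% | No country terms | Country terms |
|---|---|---|
| GEE, country-specific correlations, uncorrected sandwich, z test | 7.9% to 9.7% | 12.0% to 13.5% |
| Same, Kauermann-Carroll correction with t | 6.4% to 8.2% | 9.7% to 10.5% |
| GEE, one common correlation, uncorrected | about 1.4% | 6.8% to 7.5% |
| Same, Kauermann-Carroll correction with t | about 1% | about 5% to 6% |
| Cluster-level linear model with site terms | – | about 5% to 6% |

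With country terms the t reference has 58 clusters − 5 country terms − 1 treatment term = 52 df. Allowing slightly negative correlations raised the top-right figure to about 14%, and a cluster-size coefficient of variation of 0.6 raised it to 14.5%.

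**Step 3: cross-check from the standard errors.** The mean standard error was about 12% (no country terms) to 21% (country terms) below the true SD. If that were the only fault, the error would be 2 × [1 − Φ(1.96 × 0.88)] = 2 × [1 − Φ(1.725)] ≈ 8.5%, and 2 × [1 − Φ(1.96 × 0.79)] = 2 × [1 − Φ(1.548)] ≈ 12%. Both agree with the table.

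**Step 4: smaller ICC.** At ICC 0.001 the uncorrected country-specific GEE gives about 7% without country terms (8.4% in a run with equal rates across countries) and 9% to 10% with them. The correction with t brings this to about 6% to 7%.

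**The case against.** The strongest reply is that the GEE is not settled as the primary test. The cluster-level procedure is named first, is the one said to produce the hypothesis test and confidence interval, and is close to nominal. This stands. A reader might infer that the trial's primary test has more than twice its stated error rate. The article does not support that, because it is true of only one of the two analyses called primary. What remains is that the GEE is also called primary and nothing marks it as supportive, so settling the conflict in its favour would select the faulty test.

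A second reply is that 'uncorrected' is read from silence. A small-sample correction and a t reference are details that an article commonly leaves to the SAP, which is not shown. This also stands, and their absence is not the point made here. The country-specific correlation is stated, however, and it is the main cause: with the correction, about 7% (no country terms) and 10% (country terms) remain at ICC 0.005.

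A third reply is that the size depends on choices the article does not make. A flat 13% is tempting but needs country terms, and the article states site adjustment only for the cluster-level analysis. The size also falls with a smaller ICC and varies with accrual period and cluster-size variation. So the figures must carry their conditions.

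**Conclusion.** The point holds, conditional on the GEE being used as the primary test. At ICC 0.005, with 500 births per cluster, Table 3 rates plus 25 near misses per 1,000 and no small-sample correction, its nominal 5% test rejects a true null about 9% of the time without country terms and 12% to 14% with them. At ICC 0.001 the figures are about 7% and 9% to 10%. A correction alone does not restore 5% at the plan's ICC.

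The cluster-level alternative is near nominal with country as the stratum (about 5% to 6%). If finer strata were modelled, taking ten as an assumption, it rose to 7% to 8%.

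**What to change.** Preferred: state that the cluster-level linear model with site terms is the only primary test, and label the GEE as supportive.

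If the GEE is kept as primary, make these changes together:

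- one common within-cluster correlation in place of five;
- fixed effects for country, because a common correlation without them is very conservative when country rates differ (about 1.4%);
- a Kauermann-Carroll-type bias-corrected sandwich variance;
- a t reference with 52 df.

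The cost is SAP wording and software options, settled before outcomes are compared by arm. Estimated power for a 20% reduction is about 80% with the corrected GEE. The uncorrected GEE shows an apparent 84% (common correlation) to 86% (country-specific), part of which comes from the inflated error rate. These power figures are simulation estimates under the same assumptions and were not repeated.
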